### Stimuli and apparatus

Auditory stimuli for both Experiment 1 (finger) and 2 (waist) will be generated through Audacity software and presented via closed headphones (Sennheiser HDA300) with high passive ambient noise attenuation (> 30 dBA). The auditory stimuli will consist of pure tones (2000 ms duration, 44.1-kHz sample rate) of increasing (‘ascending’ tone: 700 to 1200 Hz), decreasing (‘descending’ tone: 700 to 200 Hz) or constant (‘constant’ tone: 700 Hz) frequency, as [25] and [50]. An additional auditory stimulus, presented in the anchor task at the beginning of the experiment, will consist of a pure tone of constant frequency (‘anchoring’ tone: 250 ms duration, 700 Hz). A 10 ms onset/offset ramp will be added to the auditory stimuli to prevent clipping. Prior to completing both experiments, participants will adjust the volume on the headphones to a comfortable level. Figures 1 and 2 show a schematic diagram and a detailed description of each experimental setup. Both experiments will be run on a HP 15S-fq4027ns Intel Core i5 laptop. Body visualizer task will be completed on a 1920 × 1080 pixel resolution computer screen (AOC e2270swn led 21.5″) (see the S1 section A). For Experiment 1, we will use a vernier calliper (DEXTER; Range: 150 mm; Graduation: 0.001″/0.02 mm) (see the S1 section B). For Experiment 2, we will use a paediatric stadiometer (ADE MZ10028-1; Range: 100 cm; Graduation: 1 mm) (see the S1 section B).

**Fig. 1 Fig1:**
[figure not shown]
Experiment 1 experimental setup, extracted from [25]. (**a**) A vertical plastic panel (39 × 15 cm) will be attached on the bottom and right side to a vertical metal bar (2 × 2 × 50 cm). Participants will sit in front of the panel, with their right hand pressed and pulled out against it and their fingertip pointing upwards. A black cloak will be tied to the participant's neck; the other side of the cloak will be attached to the top of the panel to block the participant from seeing her own hand. (**b**) To detect the participant's finger pulling action and trigger the auditory stimulation, a force-sensitive resistor (FSR; 4 mm-diameter active sensing area) will be attached to the right index fingertip. The FSR will be connected to a computer via an Arduino microcontroller. Presentation® software (Version 18.0, Neurobehavioral Systems, Inc., Berkeley, CA, www.neurobs.com) will be employed for stimulus delivery and response recording. (**c**) A slide bar will be used to collect participants’ estimates of their fingertip and knuckle position. This apparatus consists of a ruler fixed on the right side of the metal bar, parallel to it. The ruler will be blacked out on the side facing the participant. Two horizontal clips will be mounted on the ruler, each of them with a red dot which will serve as visual points that the participant uses to mark their felt fingertip and knuckle positions. The two horizontal clips on the ruler will be initially positioned at the heights of 10 cm and 50 cm. A red fixation point will be fixed on the top centre of the plastic panel (over the cloak). Permission to reproduce the figure from: CC BY 4.0

**Fig. 2 Fig2:**
[figure not shown]
Schematic depiction of experimental procedure and timeline of events for participants with subthreshold ED symptomatology and control participants. R = Randomized order

### General experimental procedure

Table 1 shows an overview of study measures and data collection time points and Fig. 3 shows a schematic representation of the experimental procedure. After reading the information sheet and signing the information consent, participants will complete the S-EDE-Q. Participants eligible to take part will be invited to the lab at Loyola Andalucia University. The experimental procedures will be implemented, and all data will be collected, by a postgraduate Ph.D. researcher trained by senior members of the research team. After reading the information sheet and signing the information consent, demographic data (age and BMI) will be collected. Later, participants will complete two questionnaires related to the secondary aim (see Table 2). The Multidimensional Assessment of Interoceptive Awareness Scale (MAIA) (to assess interoceptive body awareness) and the Highly Sensitive Person Scale (HSPS) (to assess sensory-processing sensitivity). The same participants will complete both Experiments 1 and 2.

**Fig. 3 Fig3:**
[figure not shown]
Experiment 2 experimental setup. (**a**) The participants will sit in front of a table, with both hands pressed and pulled out against their waist. A black cloak will be tied around the participant's neck; the other side of the cloak will be attached to the bottom of the table to prevent the participant seeing their body. (**b**) Similarly to Experiment 1, to detect the task of pressing and pulling out the participant's waist and activate the auditory stimulation, a force-sensitive resistor will be placed on one finger. The FSR will interface to a computer through an Arduino microcontroller. Likewise, Presentation® software version 18.0 will be used for stimulus delivery and response recording. (**c**) A horizontal ruler will be used to collect the participants' estimates of their waist width. The ruler will be located on the table. The ruler will be dark on the side facing the participant. Two horizontal metal clips will be mounted on the ruler, each with a red dot that will serve as visual points that the participant will use to mark their waist position. A red fixation point will be placed on the middle of the table

Prior to the experiments, participants will be asked to remove any jewellery from their hands and verbal and written instructions about the tasks will be given to them. Before each experiment, anthropometric data (in centimetres, thereafter ‘cm’) will be collected (finger length and waist width). Next, participants will be accommodated in the experimental setup and equipped with the pressure sensor (fixed with rubber bands) and the headphones. First, participants will be asked to complete the “anchor” task, which consists of pressing and pulling their right index fingertip with their left hand (in Experiment 1) or pressing and pulling out their waist with their index fingertips (in Experiment 2) twenty times, an action that triggers the ‘anchoring’ tone on each occasion (as in [25]). Note that during this task, participants will not be exposed to the ‘ascending’ or ‘descending’ tones. The “anchor” task uses a standard tone to facilitate participants pair the motor action and the production of a sound [25]. Having completed the “anchor” task, participants will be asked to complete a practice task, one trial for each feedback condition. Later, participants will be asked to complete the experimental block.

The procedure and materials of each of the experimental blocks is described in next sections and in Figs. 1 and 2. In brief, in the experimental block each experimental tone (‘ascending’, ‘descending’, ‘constant’), will be presented ten times. The order in which the tones are presented will be counterbalanced across participants following a within-subject design. After the experimental block is completed, participants will be asked to repeat the task of pulling their right finger (Experiment 1) or waist sides (Experiment 2) while listening to a tone for three more trials, one trial for each feedback condition, with the presentation order randomized across participants. Participants will be asked to complete a body feelings questionnaire after each feedback condition (questionnaire block) [see Additional file 2 and 3 for more details]. Additionally, for Experiment 2, a baseline and post-experiment body size discrepancy measure will be collected. The full experimental procedure will take approximately 120 min with a 5-min rest interval between both experiments. After completing the study, a debriefing session will be carried out.

#### Experiment 1 procedure: Finger

First, the length of the index finger of the participant’s right hand will be measured by the experimenter using a vernier calliper from the proximal crease at the base of the finger to the tip of the finger. Next, participants will be required to complete an "anchor" task. In this task, participants will be asked to press and pull out their right index fingertip with their left hand twenty times, an action that will trigger the ‘anchoring’ tone on each occasion. After completing the anchor task, participants will complete a practice task, one trial for each feedback condition.

In each practice trial, participants are required to stare straight at the red fixation point and complete the simple action of pressing and pulling their right index fingertip with their left hand while keeping the right index finger in a fixed position (straight against the plastic panel and metal bar, see Fig. 1). One of the three experimental tones ('ascending,' 'descending,' or 'constant') is triggered by the pressing/pulling action. Participants are instructed to continue pressing and pulling their fingers until the sound is no longer audible and, once the sound stops, to relax their left hand while continuing to grasp their right finger with the left hand. They will be then asked to estimate the position of their right fingertip and knuckle by having the experimenter adjust the two visible points on the ruler clips. This adjustment will be done as follows: First, the experimenter will move the top clip downwards at a continuous speed until the participant indicates that the visual point on the clip has reached the fingertip position with a "*Stop*" signal. Following a similar procedure, the experimenter will move the bottom clip upwards at a continuous speed until the participant indicates that the visual point on the clip has reached the knuckle position with a "*Stop*" signal.

Additionally, for each estimation (fingertip and knuckle), the feeling of confidence with the estimations made will be assessed.

The experimenter will use the measurements on the back of the ruler to record the fingertip and knuckle positions, rounding to the nearest 0.5 cm. After each trial, the clips are relocated. After completing the practice task, the experimental block will begin. Participants will repeat the task for thirty trials. Each experimental tone will be presented ten times. The order of trials will be randomized across participants. Participants will be given the opportunity to rest after each 10 trials.

After the experimental block, participants will be asked to repeat the task for three more trials (one for each sound condition, their order randomized across participants), in order to collect self-report measures (questionnaire block). After each trial, participants will complete a questionnaire that assesses their subjective experience during the task [see Additional file 2].

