In each practice trial, participants are required to look straight at the red fixation point in the middle of the table and complete the simple action of pressing and pulling their waist with both hands while keeping them fixed to their waist (see Fig. 2. One of the three experimental tones ('ascending,' 'descending,' or 'constant') is triggered by the pressing and pulling action. Participants are instructed to continue pressing and pulling their hands until the sound is no longer audible and, once the sound stops, to relax both hands (while keeping touching their waist). They will then be asked to determine the width of their waist by having the experimenter adjust the two visible points on the ruler clips. As a paradigmatic example, this adjustment will be done as follows: as in Keizer et al. [18], first, the experimenter will move both clips closer together at a continuous speed until the participant indicates that the clips have reached the perceived waist width position with a "Stop" signal. Similarly, the starting point of the aperture width (A) will be set at A = 2.0 × W (W = waist width in cm). This will be repeated while the clips are closed, and while the experimenter pressed and pulled them apart. The initial position of the clips will be counterbalanced across the trials. For both conditions we will collect waist width estimation measurements. Similarly, for each condition, the feeling of confidence with the estimation will be assessed and an average score will be obtained.

As in the finger experiment, the experimenter will use the measurements on the back of the ruler to record the position of the clips, rounding to the nearest 0.5 cm. After completing the practice task, the experimental block will begin. They will repeat the task for thirty trials. Each experimental tone will be presented ten times. The order of the trials will be randomized among participants. Participants will have an opportunity to rest after each 10 trials.

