### Data management

#### Estimation of body position/size and confidence task

For both experiments, data from the 10 repetitions for each condition will be averaged. As a rule of thumb, for participants with one trial per condition excluded, data for that trial will be replaced by the mean value of the other nine trials for that condition (as in [25]). Conversely, participants with more than one trial per condition excluded, will be excluded from all analyses. Overall, data from trials exceeding three standard deviations from the mean group value will be excluded.

For Experiment 1, we will collect measures for estimated knuckle position and fingertip position, as well as level of confidence with each estimation. In addition, for each trial, the estimated knuckle position will be subtracted from the estimated fingertip position in order to calculate the estimated finger length (as in [25]). For Experiment 2, we will collect waist width estimations, as well as level of confidence with each estimation. For each trial, we will estimate the perceived waist width by averaging the two responses given by the participant (i.e., for the opening and closing aperture).

For each participant a total of 12 summary scores will be calculated [(knuckle position + fingertip position + finger length + waist width limits) × (3 feedback conditions: ‘ascendent’, ‘constant’, ‘descendent’)]. Similarly, a total of 12 summary scores for the confidence task will be calculated [(confidence knuckle position + confidence fingertip position + confidence finger length + confidence perceived waist width limits) × (3 feedback conditions: ‘ascendent’, ‘constant’, ‘descendent’)].

Data from Presentation® software (Version 18.0, Neurobehavioral Systems, Inc., Berkeley, CA, www.neurobs.com) will be recorded into a file in UTF-8 format. The file will be organized and imported into Microsoft Excel 2021 and subsequently into IBM SPSS Statistics version 28.0. Data generated associated with the anchor tasks and practice tasks will be disregarded.

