### Sample size considerations

As these analyses are intended to generate future confirmatory hypotheses, no sample size calculation was conducted. As Jones et al. [53] noted, sample size calculation may be of little value in early exploratory studies where there is a lack of previous research. In an exploratory study, the primary focus is on generating new research questions, identifying patterns and trends, and identifying potential areas for further research, rather than on testing a specific confirmatory hypothesis. As such, the sample size in an exploratory study may not be determined based on statistical power or precision and could be relatively small. Instead, the sample size may be based on the need to obtain a sufficient amount of data to allow for the exploration and identification of meaningful patterns and trends.

In this regard, a total of 100 participants (50 participants in each group) will allow us to gain an exploratory understanding between body perception and non-naturalistic auditory information in participants with subthreshold ED symptomatology. This sample size is the minimum recommended by Brysbaert [54] to seek differences between groups and is also between 30 and 150 participants, that is the sample size usually recommended in exploratory study designs with non-probability sampling [55]. To this end, and based on norms for the Spanish version of the Eating Disorders Examination Questionnaire (S-EDE-Q), we will screen approximately at least 450 young adult females [39].

Due to the limited sample size, we acknowledge that the statistical power for each of the hypotheses proposed in this study to detect differences between groups might not be sufficient according to the traditional standards in experimental psychology (effect size = 0.4, power = 0.80 and alpha value = 0.05) [54]. Therefore, the results should be taken with caution and should be contextualized within an exploratory framework. In case of meaningful results, the present exploratory study will provide the necessary foundation for a formal sample size calculation for a future confirmatory larger-scale study.

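### Estimated finger and waist positions are rounded to 0.5 cm without a stated reason, a modest and avoidable loss of precision

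*Protocol article*

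**What the plan says.** Under Experiment 1 procedure: Finger, the experimenter reads the back of the ruler "to record the fingertip and knuckle positions, rounding to the nearest 0.5 cm". Under Experiment 2 Procedure: Waist, the instruction is "to record the position of the clips, rounding to the nearest 0.5 cm". Neither section gives a reason for the step, and the ruler's own graduation is not stated.

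The section Estimation of body position/size and confidence task then builds the scores. For the finger, "the estimated knuckle position will be subtracted from the estimated fingertip position in order to calculate the estimated finger length", trial by trial. For the waist, "we will estimate the perceived waist width by averaging the two responses given by the participant", that is, one response with the aperture opening and one with it closing. In both experiments "data from the 10 repetitions for each condition will be averaged".

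Actual finger length and waist width are measured separately, with a calliper graduated at 0.02 mm and a stadiometer described under Stimuli and apparatus as "Graduation: 1 mm". The 0.5 cm rule is not applied to these.

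**The concern.** The estimated positions are the implicit measure of both illusions. They enter the group-by-tone ANOVAs (H2 to H4) and serve as the body-image-flexibility inputs to the correlations and regressions (H5, H6). Recording them in 5 mm steps discards information when the reading is taken, and it cannot be recovered later. Finger length takes the error twice, because it is a difference of two rounded readings.

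If perceived size shifts by only a few millimetres, the error in a single trial is of the same order as the effect. Averaging over repetitions helps only if a participant's responses scatter enough across the 5 mm grid. When they scatter little, much the same rounding error recurs from trial to trial. At stake are some power for the interaction and some attenuation of individual susceptibility scores, in a study that already concedes its power may be insufficient.

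**Working it through.** **Inputs from the protocol.** Step w = 5 mm; two readings per finger length; two aperture responses per waist width; 10 trials per tone; 50 participants per group.

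**Assumed, because the protocol gives no values.** SD per reading (s) of 1 to 5 mm; true ascending-minus-descending shift of 2 mm; between-person SD of that shift of 2 mm (3 mm in the power example).

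**The plan's own figure.** There is no sample-size calculation and no effect in millimetres to reproduce. The only benchmark, under Sample size considerations, is effect size 0.4, power 0.80 and alpha 0.05. For two groups of 50, a normal approximation gives 0.4 × √(50/2) = 2.00, so power = Φ(2.00 − 1.96) ≈ 0.52. Power of 0.80 would need 99 per group. This agrees with the protocol's own caution.

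**Rounding error at a 5 mm step**
- One reading: 5/√12 = 1.44 mm (maximum 2.5 mm).
- Single-trial finger length: 1.44 × √2 = 2.04 mm (maximum 5 mm).
- Ten-trial mean finger length, independent errors: 2.04/√10 = 0.65 mm.
- Ascending minus descending, per participant: 0.65 × √2 = 0.91 mm.
- Group-by-tone contrast: 0.91 × √(2/50) = 0.18 mm.
- Waist width, two clips and two apertures: 1.44 mm per trial, 1.44/√10 = 0.46 mm for the ten-trial mean, and 0.46 × √2 = 0.65 mm for the tone difference.

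**The same at a 1 mm step.** 0.29 mm per reading, 0.41 mm per single-trial finger length and 0.18 mm for the tone difference.

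**When errors are not independent.** The 0.91 mm figure relies on scatter across the grid. In simulation with a fixed 2 mm shift, the added error SD was about 0.9 mm for s of 2 mm or more and about 1.3 mm at s = 1 mm. The mean shift stayed unbiased.

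**Individual scores (H5, H6).** Taking the tone difference as the susceptibility score, with between-person variance 2² = 4 mm²:
- Trial-noise variance: 4s²/10 = 1.6 mm² at s = 2 and 10 mm² at s = 5.
- Rounding variance: 0.91² = 0.83 mm².
- s = 2 mm: squared correlation with the true shift 4/5.6 = 0.71 unrounded and 4/6.43 = 0.62 rounded. The variance rises by 0.83/5.6 = 15%.
- s = 5 mm: 4/14 = 0.29 unrounded and 4/14.83 = 0.27 rounded. The variance rises by 0.83/14 = 6%.
- s = 1 mm (simulated, because the independence formula no longer applies): 0.91 unrounded and about 0.71 rounded.
- Recording to 1 mm stays within about 0.01 of the unrounded value in each case.

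**Group contrast (H2 to H4).** Set d = 0.4 before rounding, between-person SD 3 mm and s = 2 mm. The variance goes from 9 + 1.6 = 10.6 to 11.43 mm², so d becomes 0.4 × √(10.6/11.43) = 0.385. Then 0.385 × 5 = 1.93, and power is Φ(1.93 − 1.96) ≈ 0.49. Simulation gave 0.51 falling to 0.48 at s = 2 mm, 0.49 at 5 mm and 0.46 at 1 mm.

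**The case against.** The strongest reply is that this is a small matter. The hand is hidden, and the experimenter moves a clip by hand until the participant says stop. Scatter of at least a few millimetres between trials is easy to believe, and then the rounding error averages down as shown. The study calls itself exploratory, and its setup follows the earlier finger study (reference 25), so keeping to its method has some value. A 0.02 mm calliper reading of anatomy also sets no standard for a hand-stopped perceptual judgement. All of this stands, and it is why the point is rated low.

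A reader might infer that rounding could hide the illusion altogether, leaving many participants with no recorded shift. That needs near-perfect repeatability across ten trials. It is a mathematical limit, and nothing in the protocol suggests it will be met. A reader might also infer that all finger and waist measurements are coarsened, but the rule covers estimated positions only. Nor does the error of about 2 mm for a single trial apply to the analysed scores, which are ten-trial means.

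What the reply does not supply is a reason to prefer 0.5 cm. Comparability does not require it, since finer data can be rounded afterwards and coarse data cannot be refined.

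**Conclusion.** The point holds as a modest loss of precision, without bias and without contradiction in the text. Rounding adds an error SD of about 0.9 mm to each participant's tone difference in finger length at an SD per reading of 2 mm or more, and about 1.3 mm at 1 mm. The waist error is smaller, about 0.65 mm with independent errors.

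For H2 to H4 the cost is a few points of power at most unless responses are very consistent. For H5 and H6 the attenuation is somewhat larger when s is near 2 mm or below, and slight at 5 mm, where trial noise dominates and finer reading would not help much. All these sizes depend on assumed trial and between-person SDs, and the H5 and H6 figures also assume that the tone difference is the score used. "Avoidable" assumes that the ruler carries marks finer than 0.5 cm.

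**What to change.** In both procedure sections, replace the 0.5 cm rule with recording to the nearest 1 mm, or to the ruler's finest graduation, and state that graduation. If comparison with reference 25 is wanted, round the recorded values to 0.5 cm afterwards as a sensitivity analysis. If 0.5 cm is kept, give the reason.

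The cost is one wording change in each of two places and slightly slower reading per trial. It needs no extra trials or participants, and no new equipment if the ruler has millimetre marks.
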